### Outcomes measure

3.5

Study outcomes will be evaluated in accordance with Table 1. Primary and secondary outcomes are measured at baseline, and at 2-months, 4-months, and 6-months after baseline. For ethical reasons, if the intervention is found to be effective, all groups will have access to IVRS at the end of the intervention. Primary outcome will be immunosuppressive medication adherence that is evaluated based on a self-report in both groups during the follow-up period. The secondary outcomes include transplant knowledge, HRQoL, and rehospitalization rate.

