### Participants

3.3

KT recipients who will be referred to the center in July 2018 for follow up visits and caretaking are screened for eligibility. Eligible patients will be asked to provide consent with appropriate trail information and enough time to study and ask questions. Patients will be received 2 types of information related to the study:

(1)fully understandable oral information(2)2informed consent, in which the study design is described completely.

Informed consent has already been evaluated by the Ethics Committee of MUMS (IR.MUMS.fm.REC.1396.160). We ensure participants can withdraw from the study at any time without any commitment and no effect on their subsequent care. Eligible participants will be included after completing informed consent.

The inclusion criteria are as follows:

(1)KT recipients who have received a KT between 20 March 2012 and 20 March 2017,(2)having 18 years of age or more,(3)having acceptable graft function (do not need any types of dialysis),(4)having access to a mobile phone,(5)being able to read the informed consent information, and(6)willingness to participate.

The patients who are refused to participate in the study will be excluded. KT patients will be randomly assigned to the control (usual care) or intervention (usual care plus IVRS) groups. Usual care includes an educational booklet for KT and patient education provided by the nephrologists.

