### Randomization

3.8

After reviewing the outpatient medical records of patients referred to the clinic, we first obtain their informed consent. Then participants will be stratified into different strata based on their respective date of transplantation. The first stratum will be included participants who have received a transplant between March 21, 2015 and March 20, 2017, and the second stratum will include recipients who have received a transplant between March 20, 2012 and March 20, 2015. In fact, the goal is to eliminate the effect of post-transplantation time in evaluating self-management patients. Then participants will be randomly assigned to the control or intervention group in each stratum. For generating the allocation sequence, we will be used computer-generated random numbers provided by www.randomization.com. Randomization sequence will be created by an independent researcher, who is not involved in the collection or intervention procedure. The allocation ratio of intervention: control is 1:1.

For each patient, a folded paper, containing the assignment group together with a unique identification number in the study, will be stored in a sealed envelope, such that the information will not be readable without opening the envelope. Sealed envelopes are arranged based on randomized sequences. The assistant researcher will collect the baseline questionnaire and assigns the patient to the relevant stratum. Subsequently, the assistant researcher contacts the researcher (responsible for registering the patient in the IVRS) and the researcher will assign the patient to 1 of the 2 intervention or control groups. If the participant is assigned to the intervention group, the researcher registers the participant in the IVRS based on baseline information.

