Rehospitalization was defined as any unscheduled rehospitalization (our program does not hospitalize for routine follow-up evaluation). The total number of rehospitalization days over the duration of the study, as measured by the cumulative number of hospitalization days over this time period, were extracted from the hospital information system and participants’ medical records.

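### Rehospitalization is scheduled at baseline but defined only as days accrued on study, so its baseline is zero or undefined and tests across time points say nothing about the intervention

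*Protocol article*

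**What the plan says.** **Schedule.** Protocol article, section 3.5 (Outcomes measure): "Primary and secondary outcomes are measured at baseline, and at 2-months, 4-months, and 6-months after baseline". No outcome is exempted. The same section states: "The secondary outcomes include transplant knowledge, HRQoL, and rehospitalization rate". It also says "Study outcomes will be evaluated in accordance with Table 1"; the body of that table is not in the text available for this review.

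**Definition.** Section 3.10 (Data collection tools): "Rehospitalization was defined as any unscheduled rehospitalization". The quantity recorded is "The total number of rehospitalization days over the duration of the study", cumulated over that period. No window before enrolment is given. The data "were extracted from the hospital information system" and from the medical records.

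**Analysis.** Section 3.12 (Statistical analysis) handles quantitative variables by comparing time points, with repeated-measures ANOVA if they are Gaussian and the Friedman test if not. It also plans logistic and multinomial models to deal with confounding, without listing covariates.

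**Population and allocation.** Section 3.3 (Participants) admits "KT recipients who have received a KT between 20 March 2012 and 20 March 2017", screened in July 2018. Section 3.8 (Randomization) stratifies on transplant date, and "The allocation ratio of intervention: control is 1:1".

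**The concern.** The schedule asks for a baseline value of a quantity that, as defined, starts to accrue only when the study starts. Calling the outcome a rate or a number of days makes no difference, because neither form has a pre-study window.

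Two things are at stake. First, if the generic time-point analysis is applied to this outcome, it sets a structural zero against totals that cannot fall. A significant time effect would then be close to guaranteed once a few patients are admitted, in either arm and whatever the intervention does. Second, the scheduled baseline assessment tells nobody how prone to admission the two arms were at entry. That is useful for the baseline table and as a covariate for an outcome likely to be skewed, with only 60 patients planned per arm.

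**Working it through.** The article gives no admission rate, mean, SD or power for rehospitalization, so there is no planned figure to reproduce.

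**1. Baseline value.** Let D(t) be the cumulative unscheduled hospital days from study start to month t (section 3.10). Then D(0) = 0 for every patient. Change from baseline is D(6) − D(0) = D(6), so the between-arm difference is the same with or without the baseline. The baseline variance is zero.

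**2. What a time-point test does with it.** Take one arm of 60 with D at months 0, 2, 4 and 6. The assumptions are illustrative: one admission per admitted patient, with timing spread evenly over the three intervals. A patient who is never admitted is tied at all four times and contributes nothing. The ranks for the others are:
- first interval: 1, 3, 3, 3
- second interval: 1.5, 1.5, 3.5, 3.5
- third interval: 2, 2, 2, 4

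Suppose four patients are admitted: two in the first interval and one in each of the others. Deviations from the mean rank of 2.5, summed by time point, are −4.5, −0.5, 1.5 and 3.5.
- Sum of their squares: 20.25 + 0.25 + 2.25 + 12.25 = 35.
- Sum of squared individual deviations: 3 + 3 + 4 + 3 = 13.
- Tie-corrected Friedman statistic: (4 − 1) × 35 / 13 = 8.08 on 3 degrees of freedom, p = 0.044.

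In 2,000 simulated arms of 60 with random admission intervals, the test was significant in 87% of runs when each patient had a 10% chance of admission, and in over 99% at 20%. No intervention effect was simulated.

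**3. Is the between-arm comparison biased without a baseline?** On-study days were simulated with strong heterogeneity between patients (assumed gamma with shape 0.5 and scale 2, Poisson days), 60 per arm, no effect, and an unadjusted Mann-Whitney test. Over 5,000 runs the type I error was 0.048 against a nominal 0.05. The comparison is valid.

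**4. What a real baseline would add.** With correlation r between prior and on-study days, linear adjustment leaves a fraction 1 − r² of the residual variance. The article gives no r, so a range is shown:

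| Assumed r | Variance left | Variance removed |
|---|---|---|
| 0.2 | 0.96 | 4% |
| 0.3 | 0.91 | 9% |
| 0.5 | 0.75 | 25% |
| 0.7 | 0.51 | 49% |

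On the standard-error scale, r = 0.3 gives √0.91 = 0.95 and r = 0.5 gives √0.75 = 0.87.

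**5. Is a 6-month look-back available for everyone?** The latest eligible transplant date is 20 March 2017 (section 3.3). From then to 1 July 2018 is 468 days, or 15.4 months. A 6-month look-back from 1 July 2018 begins on 1 January 2018, which is 287 days, or 9.4 months, after that transplant. All other eligible patients were transplanted earlier, and later enrolment only lengthens the gap. The window therefore begins well after the transplant date for every patient, so the transplant admission should not fall in it.

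**The case against.** The strongest reply is that the specific definition overrides the general sentence. The schedule in section 3.5 fits the questionnaires, and a sensible reader would take rehospitalization as accrued on study. Timing is referred to Table 1, which may give this outcome its own row. Section 4 (Results) names only the BAASIS, SF-12V2 and K-TUT scores as compared between baseline and end of study, and the time-point sentence in section 3.12 does not name rehospitalization. A look-back covariate for a secondary outcome is also the kind of detail a condensed article may leave to the full plan.

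Much of this stands. The conflict is shown only for the text of sections 3.5 and 3.10, and applying the Friedman test to this outcome is an inference from a generic sentence. Even so, the schedule makes no exception, and the article offers no other method for a quantitative outcome. A separate row in Table 1 would still leave section 3.5 needing correction.

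A reader might go further and infer that a chance excess of admission-prone patients in one arm would bias the comparison, or that earlier admissions cannot be taken into account. The documents support neither. Days accrued after 1:1 randomisation can be compared without a baseline, and chance imbalance is already covered by the error rate of the test. The hospital records are a named source that nothing restricts to the study period, and the covariates of the regression models are left open. Prior admissions are not provided for, but they are not out of reach.

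**Conclusion.** The point holds as an inconsistency between schedule and definition for one secondary outcome. As written, the baseline value is zero or undefined for all patients, and any baseline-to-follow-up or time-point test of it is uninformative. The Friedman illustration rests on assumed admission patterns; its direction does not, because cumulative days cannot fall.

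The randomised comparison of on-study days is unaffected in validity. The loss is a check on balance and some precision: roughly 9% to 25% of residual variance at an assumed correlation of 0.3 to 0.5. That range is not from the documents, and the formula is a linear-model approximation for an outcome that is probably skewed. The primary outcome and the sample size are not touched. The correction is worth making because it is cheap, with the reservation that Table 1 could not be read.

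**What to change.** 1. Reconcile section 3.5, section 3.10 and Table 1: state that rehospitalization accrues from randomisation to month 6 and is compared between arms.
2. State in section 3.12 that this outcome does not enter the repeated-measures or Friedman comparison of time points with a zero baseline.
3. Define its baseline value as unscheduled admissions and hospital days in the 6 months before randomisation, taken in the same way for both arms from the hospital information system and medical records. Report it in the baseline table and name it as a prespecified covariate in the between-arm comparison.

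Items 1 and 2 are the necessary correction and cost only wording. Item 3 is an improvement in precision; it costs a longer date range in an extraction already planned and one more covariate, with no added patient contact.

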**Table 1 T1:**

Timing of outcome measurement and validated instrument.

### Sample size

3.6

According to the study by Garcia et al,^[35]^ an study effect size based on 90% power and data with a 2-tailed *α* = 0.05, in medication adherence between the control and intervention groups, was estimated to be 40 patients in each group. Considering the 50% prop up rate during the study, our goal is to employ 60 patients in each group.

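### Sixty per group does not cover a 50% drop-out: 30 per group remain rather than the 40 required, and the stated 90% power falls to about 80%

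*Protocol article*

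**What the plan says.** Section 3.6 (Sample size) of the protocol article builds the target in two steps.

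- **Required number.** The calculation uses "an study effect size based on 90% power" and "2-tailed *α* = 0.05" for the difference "in medication adherence between the control and intervention groups". The result "was estimated to be 40 patients in each group". The effect itself is attributed to a cited study and is not given.
- **Recruitment target.** The next sentence reads: "Considering the 50% prop up rate during the study, our goal is to employ 60 patients in each group".

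The Randomization section (3.8) confirms equal groups: "The allocation ratio of intervention: control is 1:1". No other section gives a different loss rate, evaluable number or target. The Outcomes measure section (3.5) names self-reported immunosuppressive adherence as the primary outcome, so this calculation is the one for the main comparison.

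**The concern.** The phrase *prop up rate* is almost certainly a slip for drop-out rate. It is a rate that applies during the study, and it stands between the required number and a larger enrolment number, where an attrition allowance normally goes. On that reading the three figures (40, 50%, 60) do not agree, because half of 60 is 30.

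This matters because the trial claims 90% power for its primary outcome. If attrition were as high as the plan allows for, the trial would not have that power, and a null result would be judged against a claim the design does not meet. Attrition is a real prospect here: the Interventions section (3.4) allows withdrawal at any time and removal after more than two missed follow-up visits.

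**Working it through.** **Inputs, all from sections 3.6 and 3.8:** two-sided α = 0.05; power 90%; 40 evaluable per group; 50% loss (reading *prop up* as drop-out); target 60 per group; 1:1 allocation. The effect size is not stated, so it is back-solved below as whatever effect gives 90% power with 40 per group.

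**1. Reproduce the plan's figure.**

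- Multiplying by (1 + loss): 40 × (1 + 0.50) = 60. This is the stated target.
- Dividing by the retained fraction: 40/(1 − 0.50) = 80. This is the number that leaves 40.

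The stated 60 comes only from the first form.

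**2. What 60 per group delivers.**

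- Evaluable at 50% loss: 60 × (1 − 0.50) = 30 per group.
- Largest loss that still leaves 40: 1 − 40/60 = 33.3%.
- Shortfall if 50% loss is expected: 80 − 60 = 20 per group (160 against 120 in total).

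**3. Power with 30 per group, normal approximation.**

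- Non-centrality for 90% power at two-sided 0.05: 1.960 + 1.282 = 3.242.
- It scales with the square root of the group size: 3.242 × √(30/40) = 2.807.
- Power = Φ(2.807 − 1.960) = Φ(0.847) = 0.80.

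**4. The same step by other methods**, each with the effect set to give 90% at 40 per group:

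| Method | Effect assumed | Power, 40 per group | Power, 30 per group |
|---|---|---|---|
| Two means, normal approximation | standardised difference 0.725 | 90% | 80.2% |
| Two-sample t-test | standardised difference 0.734 | 90% | 79.8% |
| Two proportions | 50% v 83.3% | 90% | 79.6% |
| Two proportions | 20% v 54.1% | 90% | 79.6% |

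For two proportions, control rates of 10%, 20%, 30%, 40%, 50% and 60% all gave 79.6%. This agreement is expected, because the effect is fixed by the 90% condition. It shows that the relative drop does not depend on the unknown effect. It does not show that 40 was the right starting number.

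**The case against.** The strongest objection is to the reading. The section never uses the word drop-out, and *prop up by 50%* could mean that the sample was simply enlarged by half. Then 40 × 1.5 = 60 is correct arithmetic, no 50% loss is assumed, and the design tolerates 33%. But a rate that applies during the study describes something that happens to enrolled patients, not a margin added beforehand. Even if the margin was meant, the sentence still needs changing, since no reader could take a tolerated loss of 33% from it.

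Three further points have some weight.

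- **The power loss is conditional.** It needs 50% actual loss. At 20% loss, 48 per group remain, and power for the same effect is Φ(3.242 × √(48/40) − 1.960) = Φ(1.591), about 94%. This stands, and it is why the corrected text should state the condition.
- **Patients who drop out may still contribute.** Adherence is also measured at 2 and 4 months, and the logistic models in the Statistical analysis section (3.12) need not be limited to 6-month completers. Some power could be recovered. However, the sample size section claims no such credit, and the repeated-measures ANOVA and Cochran test also named there usually need complete cases.
- **Eighty per cent power is widely accepted.** True, but the article states 90%, and the figure should be one the design delivers under its own assumption.

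**Conclusion.** The concern holds. Under the plan's own 50% rate, 60 per group leaves 30 evaluable, not 40. Power for the planned effect is then about 80% (79.6% to 80.2% by method) instead of 90%, and the type II error goes from 10% to about 20%.

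This rests on three assumptions: that *prop up rate* means drop-out rate; that attrition reaches the stated 50%; and that patients lost add no information to the primary comparison. The base figure of 40 is taken as given, because it cannot be checked without the effect size. The finding is therefore the relative drop from 90% to 80%, not the trial's true power.

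**What to change.** The sponsor should first say what the 50% was meant to be, and write drop-out rate if that is what was intended. Then choose one of two corrections.

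1. **Keep 60 per group and restate the power (preferred).** Suggested text: *Forty evaluable patients per group are required for 90% power. Enrolling 60 per group preserves this if attrition does not exceed 33%. If attrition reaches 50%, 30 per group remain and power is about 80% for the same effect.* This costs one sentence and a less favourable power statement. No extra patients are needed, and allocation, outcomes and analysis are unchanged.
2. **Enrol 80 per group**, if 50% loss is really expected and 90% power is to be kept. This costs 20 more patients per group, 40 in all. The Results section (4) says recruitment was not complete, so this was still open when the article was written.

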### Participant timeline

3.7

Participants’ timeline will be done based on Table 1. In the baseline assessment, we asked patients about the suitable timing to receive educational calls.

### Randomization

3.8

After reviewing the outpatient medical records of patients referred to the clinic, we first obtain their informed consent. Then participants will be stratified into different strata based on their respective date of transplantation. The first stratum will be included participants who have received a transplant between March 21, 2015 and March 20, 2017, and the second stratum will include recipients who have received a transplant between March 20, 2012 and March 20, 2015. In fact, the goal is to eliminate the effect of post-transplantation time in evaluating self-management patients. Then participants will be randomly assigned to the control or intervention group in each stratum. For generating the allocation sequence, we will be used computer-generated random numbers provided by www.randomization.com. Randomization sequence will be created by an independent researcher, who is not involved in the collection or intervention procedure. The allocation ratio of intervention: control is 1:1.

For each patient, a folded paper, containing the assignment group together with a unique identification number in the study, will be stored in a sealed envelope, such that the information will not be readable without opening the envelope. Sealed envelopes are arranged based on randomized sequences. The assistant researcher will collect the baseline questionnaire and assigns the patient to the relevant stratum. Subsequently, the assistant researcher contacts the researcher (responsible for registering the patient in the IVRS) and the researcher will assign the patient to 1 of the 2 intervention or control groups. If the participant is assigned to the intervention group, the researcher registers the participant in the IVRS based on baseline information.

### Blinding

3.9

Because of the nature of the study, the allocation of participant to the control or intervention group cannot be completely blind. However, physicians and outcome evaluators will be completely blinded to the control and intervention group. Hospital staff who provide clinical and educational care and treatment services to patients will also be blinded to the allocated group. Researchers other than those in the clinical trial team and the research assistant (who will register the participants and evaluate the baseline) will be blinded to the group allocation throughout the study.

### Data collection tools

3.10

BAASIS^[31]^ is a self-report tool containing 4 items for measuring adherence to immunosuppressive medications over the past 4 weeks. This tool has important dimensions such as non-adherence to medication (missing a dose), continuous missing of several doses, non-adherence to medication taking time (deviation more than 2 hours from the exact time), and reducing the doses. The patients were asked to respond on a 6-point Likert scale including 0 = *never*, 1 = *once a month*, 2 = *every 2 weeks*, 3 = *every week*, 4 = *more than once a week*, and 5 = *every day*. Patients selecting an answer other than “never” were considered as non-adherent. This tool was translated into Persian using the forward–backward translation method. Then another specialist compared the new version with the old version, and the incompatibilities were removed. The revised version was ultimately approved by the translators, and the final draft was prepared.

Patients’ transplant knowledge treatment process will be measured using the kidney transplant understanding tool (K-TUT).^[29]^ This questionnaire was first translated to Persian by 2 researchers (forward) and then back-translated by 1 individual (backward). Questionnaire's content validity was checked through 1 round of a Delphi session with the participation of 4 nephrologists and 4 coordinator nurses. To assess content validity quantitatively, the content validity index (CVI) and content validity ratio (CVR) indices were used. CVI was computed as the number of experts giving a rating 3 or 4 to the relevancy of each item, divided by the total number of experts. In order to determine CVR, the experts were asked to examine each item based on a 3-part spectrum: it is “necessary,” “useful,” and “not necessary,” Then the responses were evaluated according to the formula (the number of specialists selecting the “necessary” option divided by the total number of the specialists). Items with CVI values less than 0.78 were deleted. The questionnaire reliability was checked through test-retest reliability analysis. The questionnaire was given to 25 recipients. After a week they were asked again to answer the questions, and Pearson Correlation Coefficient was calculated for patient's transplant knowledge scores. This coefficient was 0.72, indicating the questionnaire acceptable level of reliability. The final questionnaire contained 9 true/false and 13 multiple choice questions (more than 1 correct answer). One score was given to each correct answer. The maximum knowledge score was 57. Higher knowledge scores indicated more KT knowledge.

In order to assess the health-related quality of life, the 12-item short form survey, second version (SF-12V2) questionnaire was administered. This questionnaire was validated by Montazeri et al for a group of Iranian patients.^[36]^ This 12-item questionnaire evaluates a general understanding of your health, physical performance, physical health, emotional problems, physical pain, social function, vitality and vital energy, and mental health. The maximum quality of life score is 48. A score greater than 37 indicates a good quality of life, a score between 25 and 36 indicates intermediate quality of life, and a score less than 24 indicates poor quality of life.

Rehospitalization was defined as any unscheduled rehospitalization (our program does not hospitalize for routine follow-up evaluation). The total number of rehospitalization days over the duration of the study, as measured by the cumulative number of hospitalization days over this time period, were extracted from the hospital information system and participants’ medical records.

